## Background

Yearly, approximately 90,000 critically ill patients are admitted to Dutch intensive care units (ICU) [1]. During their time in the ICU many patients are exposed to adverse experiences; acute pain being a leading stressor [2]. Physical and psychological stresses caused by pain have been associated with increased length of stay, morbidity and poor mental health outcomes [3–5], and affect quality of life even after ICU discharge [6, 7]. Interview studies revealed that almost half of ICU patients experience moderate to severe pain both at rest as well as during procedures [8–11]. There remains a large gap between ideal and actual care with respect to pain management in intensive care, making it a suitable target for quality improvement (QI) strategies, such as audit and feedback (A&F) [12–15]. A&F has been defined as a “summary of clinical performance in a specific area with or without recommendations for action” [16] and aims to support physicians in accurate self-assessment [17].

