### Statistical analysis

Descriptive statistics will be calculated for all variables of interest. Categorical variables will be summarised using counts and percentages. We will use mixed-effects logistic regression analysis for the main analysis in both parts of the study.

To assess the influence of A&F on self-assessments and improvement intentions (laboratory experiment in part 1), we will use a binary “A&F received” covariate. To adjust for correlations between repeated observations within participants we will add a random intercept for “participating professional”. To adjust for clustering effects within ICUs and around quality indicators, we will add random intercepts for “ICU” and “quality indicator”.

To assess the effect of receiving the action implementation toolbox on pain management performance (RCT in part 2), we will use “patient shift” as unit of analysis. We will include the covariates time, study arm and the interaction term time × study arm, while adding random effects to adjust for clustering within ICUs, patients and shifts. If we suspect problems with the randomisation, we will perform tests of imbalance between groups in baseline variables that may influence the outcome, i.e. age, gender, length of stay and severity of disease at patient-level and hospital type and ICU-level. In case of an imbalance (above 5% level for statistical significance), we will conduct a sensitivity analysis adjusted by these variables to test the robustness of our methods [55].

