There are some limitations relating to the selection of participants in our study. Eligible ICUs are participating in the NICE registry, are capable of submitting the data items for the quality indicators and agree to allocate a QI team. These criteria may lead to the selection of a non-representative sample of ICUs, because eligible facilities are less likely to be understaffed and more likely to have information technology support to facilitate routine collection of NICE data. Therefore, the generalisability of our findings may be limited to ICUs that are motivated and equipped to systematically monitor and improve the quality of care they deliver. However, as information technology support are rapidly improving in most hospitals, we believe that this will be of less concern in the future. Finally, there is some evidence that non-teaching hospitals use pain assessment tools more often than teaching hospitals [12]. Even though applying a stratification method according to hospital type would equalise the distribution of hospital types over the two arms in the RCT (study part 2) and thus prevent confounding by this variable [63], we expect there will be insufficient participants to do so. Therefore, in case of an imbalance between arms at baseline, we will assess the robustness of our findings by means of a sensitivity analysis.

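### The adjusted sensitivity analysis has two conflicting triggers, relies on a test with little power for hospital type, and counts length of stay as a baseline variable

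*Protocol article*

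**What the plan says.** The main model for the cluster trial is fixed in advance in the Statistical analysis section: "We will include the covariates time, study arm and the interaction term time × study arm", with random effects for clustering. It contains no hospital type and no patient characteristics.

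Adjustment is a second step with two gates. The first is "If we suspect problems with the randomisation, we will perform tests of imbalance between groups in baseline variables that may influence the outcome". The second is "In case of an imbalance (above 5% level for statistical significance), we will conduct a sensitivity analysis adjusted by these variables". The variables are "age, gender, length of stay and severity of disease at patient-level and hospital type and ICU-level", where the last words evidently mean hospital type at ICU level.

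The Strengths and limitations section returns to hospital type. It reports that "there is some evidence that non-teaching hospitals use pain assessment tools more often than teaching hospitals", accepts that stratifying by hospital type would prevent confounding by it, and declines to stratify because too few ICUs are expected. It relies instead on a sensitivity analysis whenever the arms are imbalanced at baseline. It mentions neither suspicion nor a significance test.

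On length of stay, the Background says: "Physical and psychological stresses caused by pain have been associated with increased length of stay".

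**The concern.** Three features of the rule work against its purpose.

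- **The trigger is stated in two ways.** Under one section, a chance imbalance in hospital type leads to no adjusted analysis unless someone suspects the randomisation. Under the other, the imbalance is enough. No criterion for suspicion is given, and the Randomisation and allocation section says the investigators cannot be blinded.
- **The significance test is a poor gate.** After a sound randomisation it measures only chance. With about 24 ICUs it rarely reaches 5% for an ICU-level variable, however prognostic that variable is.
- **Length of stay is not a baseline variable** for a patient admitted after the ICU was allocated. If better pain management shortens stay, adjusting for stay conditions on a possible consequence of the intervention.

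At stake is the check that the article offers in place of stratification. It may not be run when it is needed, and when it is run it may differ from the main result for a reason unrelated to baseline imbalance.

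**Working it through.** **Inputs**

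- 24 ICUs (Sample size), allocated 1:1 without strata (Randomisation and allocation), so 12 v 12.
- 32 of 83 registry ICUs are teaching units (Setting): 32/83 = 38.6%, and 0.386 × 24 = 9.3. I take 9 of 24, which assumes that participation follows the registry mix.
- Threshold 5% (Statistical analysis). No test is named, so I show Fisher's exact test and the uncorrected chi-square.

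The article gives no figure for this rule that could be reproduced. The 24 ICUs are only an input here. I reach that total with an SD of 5 points and a net difference of 10 − 4.3 = 5.7 points: 4 × (0.05 × (1.960 + 0.842)/0.057)² = 24.2. Nothing below depends on that reading.

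**How often chance splits arise**

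With X teaching ICUs in one arm, P(X = k) = C(9,k) × C(15,12−k) / C(24,12), and C(24,12) = 2,704,156. Block structure is ignored. The counts in each direction are 420,420 (6:3), 108,108 (7:2), 12,285 (8:1) and 455 (9:0).

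- 6:3 or worse: 2 × (420,420 + 108,108 + 12,285 + 455) / 2,704,156 = 0.400
- 7:2 or worse: 2 × (108,108 + 12,285 + 455) / 2,704,156 = 0.089
- 8:1 or worse: 2 × (12,285 + 455) / 2,704,156 = 0.009

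**What a 5% test flags**

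The two-sided Fisher p-value equals the tail probability above. The chi-square is 24 × (ad − bc)² / (12 × 12 × 9 × 15).

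| Split of 9 teaching ICUs | ad − bc | Chi-square | p, chi-square | p, Fisher |
|---|---|---|---|---|
| 6:3 | 36 | 1.60 | 0.21 | 0.40 |
| 7:2 | 60 | 4.44 | 0.035 | 0.089 |
| 8:1 | 84 | 8.71 | 0.003 | 0.009 |

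Fisher therefore flags 0.9% of allocations and chi-square 8.9%, whereas 40% are at 6:3 or worse.

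The assumed mix does not drive this. With 12 teaching ICUs of 24, an 8:4 split gives Fisher p = 0.22 and chi-square p = 0.10. A split of 8:4 or worse arises in 22% of allocations, and either test flags only 3.9%.

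**Possible size**

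A 6:3 split is a difference in mix of 3/12 = 25 percentage points. With an assumed gap in performance between hospital types of 5 to 15 points, a plain comparison of levels shifts by 0.25 × 5 = 1.25 to 0.25 × 15 = 3.75 points. For 8:4 (4/12) the shift is 1.7 to 5.0 points. The article gives no gap, so this only illustrates scale, and it does not carry over directly to the planned model (see the objection).

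**Timing of length of stay**

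ICUs are randomised and then take part for 6 to 9 months (Procedure for part 2). The unit of analysis is the patient shift, so patient-level adjustment uses the stay of patients treated during the trial. That stay is complete only at discharge, under the allocated intervention. By the Background's own account, stay may lie downstream of pain. Age, gender and severity measured at admission do not have this problem.

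**The case against.** The strongest reply is that the primary result is protected. The main model is fixed, and the tests decide only whether a sensitivity analysis is run. A reader might infer that a treatment effect could be adjusted away in the main result, or that unblinded investigators could change the primary estimate. The article supports neither. This stands and limits the harm.

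Second, testing baseline balance only when the randomisation is in doubt is more defensible than routine testing, because the null hypothesis is then no longer true by design. That is fair, but it does not fit the use made of the analysis in Strengths and limitations, where the worry is ordinary chance imbalance after a sound randomisation.

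Third, leaving hospital type out need not bias the main result. If pre-feedback shifts are in the model, the arm term and ICU intercepts take up a constant difference in level, and the toolbox effect is read from time × arm. This stands too. The remaining concern is mainly hospital types that respond differently to feedback. That is plausible, since the Background says feedback may work better where baseline performance is low.

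Some stronger readings fail:

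- A 7:2 split does not necessarily go unflagged. Fisher misses it, but the uncorrected chi-square does not.
- Very high false-trigger rates for the patient-level tests would require that those tests ignore ICU clustering and would need an assumed intracluster correlation. The article states neither.
- The phrase about being above the 5% level could be taken as p > 0.05. In context it means significant at 5%; the wording is loose but the rule is not reversed.
- Length of stay is not shown to be a mediator between toolbox and pain management. The Background places it downstream of pain.

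**Conclusion.** The concern holds for the adjusted sensitivity analysis.

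- The two sections give different triggers and must be reconciled.
- A 5% test on 12 v 12 ICUs has little power for the one variable that the article names as a possible confounder. With 9 of 24 teaching ICUs assumed, 6:3 or worse occurs in 40% of allocations, and 6:3 passes under either test. The result at 7:2 depends on the test chosen, which the article does not name.
- Length of stay is wrongly classed as baseline, and adjusting for it can bias the sensitivity analysis. The documents give no basis for sizing that bias.

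The documents do not show that the primary estimate is biased. The figures rest on proportional participation by hospital type, on 24 ICUs being recruited, and on simple 12:12 allocation.

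**What to change.** In the Statistical analysis section:

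- Delete the suspicion condition and the imbalance tests.
- Pre-specify an adjusted analysis with hospital type, age, gender and severity at admission, whatever the observed balance. Preferably these enter the main model, with the unadjusted model reported alongside. At the least, the adjusted analysis is always run.
- Remove length of stay from the list.
- Do not add the ICU's baseline performance as a covariate if pre-feedback shifts are already in the outcome data, since the same data would then be used twice.

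In Strengths and limitations, replace the conditional promise with a reference to this pre-specified analysis, so that both sections say the same.

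The cost is wording and one or two ICU-level degrees of freedom. No new data are needed, because all the retained variables are already on the article's own list.

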### Process evaluation

We will perform a process evaluation using both quantitative and qualitative methods to gain insight in how the A&F intervention is implemented and used in clinical practice, and explore if and how implementation and use may affect the intervention’s impact [56].

For the quantitative part we will analyse usage logs of the dashboard to investigate the frequency with which the dashboard is used and by whom, and how this varies between ICUs and over time. We will also assess which areas of clinical performance (i.e. which indicators) users tend to focus on, and which feedback components (indicator details, patient subgroup analyses and patient lists) they typically access, and under which circumstances. Finally, we will study the contents of the action plans including the number of planned actions, whether those were typically selected from the action implementation toolbox or self-defined, and whether and when the actions are implemented. Analysing the usage logs of digital interventions allows us to study the intervention process quantitatively and unobtrusively [57].

For the qualitative part, we will collect data during the monthly telephone calls. Guided by quantitative summary reports drawn from the usage logs, we will investigate participants’ experiences with the dashboard, how they have implemented the dashboard into daily clinical practice (e.g. do they organise monthly team meetings to review the feedback; is the manager or intensivist involved; how much time do they invest in QI activities) and ICU- and individual-level barriers and facilitators that may affect the planning and implementation of actions or the intervention’s impact.

## Discussion

In order to learn how to design and deliver effective electronic A&F interventions, we need to understand the mechanisms of how A&F leads to improvements in clinical performance. Our study uses a theory-informed approach to investigate how A&F affects improvement intentions among ICU professionals (i.e. information–intention gap), and whether an action implementation toolbox with suggested actions and materials helps translating those intentions into action (i.e. intention–behaviour gap) in a two-armed RCT. The laboratory experiment, RCT and the comprehensive process evaluation are expected to provide insightful understanding of the mechanisms behind A&F.

### Strengths and limitations

The principal strength of our study is the extensive use of Control Theory [28] as a basis for our study objectives, design and evaluation. Although there is growing recognition that theory should play a central role in the design and evaluation of A&F interventions [27], explicit use of theory remains scarce [26, 58]. For example, the laboratory experiment (study part 1) will test the hypothesis that A&F improves self-assessments of clinical performance and hence improvement intentions; this hypothesis is typically assumed to be true in A&F studies but has not, to the best of our knowledge, been evaluated empirically. Also, while the large majority of quantitative evaluations A&F interventions solely report effects on clinical performance, our study will also explore the underlying mechanisms of A&F in an extensive process evaluation. Due to the electronic nature of our A&F dashboard, we are able to observe essential behavioural constructs such as intentions (planned actions), and behaviour change (completed actions), allowing us to quantify and study their relationships and potentially explain any outcome variation [57]. Further, because we will perform the qualitative part of our process evaluation guided by quantitative process reports, we may be able to make more effective and efficient use of our qualitative method by asking more focused questions.

We based the design of our intervention on theoretical and empirical evidence from A&F literature and carefully considered what feedback information to provide and how to present it [18, 23, 28, 30, 45, 59–62]. Although this increases the probability that the intervention as a whole will positively affect intensive care performance, we know from four decades of A&F trials that the effects are variable and often marginal [18]. Therefore, an RCT comparing the intervention to usual care would produce a limited amount of new knowledge [25]. In line with the international research agenda for A&F studies, our head-to-head comparison of different approaches to A&F delivery, with versus without action implementation toolbox, will contribute to speeding up the rate with which we identify the active ingredients of successful A&F interventions [27].

There are some limitations relating to the selection of participants in our study. Eligible ICUs are participating in the NICE registry, are capable of submitting the data items for the quality indicators and agree to allocate a QI team. These criteria may lead to the selection of a non-representative sample of ICUs, because eligible facilities are less likely to be understaffed and more likely to have information technology support to facilitate routine collection of NICE data. Therefore, the generalisability of our findings may be limited to ICUs that are motivated and equipped to systematically monitor and improve the quality of care they deliver. However, as information technology support are rapidly improving in most hospitals, we believe that this will be of less concern in the future. Finally, there is some evidence that non-teaching hospitals use pain assessment tools more often than teaching hospitals [12]. Even though applying a stratification method according to hospital type would equalise the distribution of hospital types over the two arms in the RCT (study part 2) and thus prevent confounding by this variable [63], we expect there will be insufficient participants to do so. Therefore, in case of an imbalance between arms at baseline, we will assess the robustness of our findings by means of a sensitivity analysis.

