#### Randomisation and allocation

We will randomly allocate participating ICUs to receive “A&F only” or “A&F with action implementation toolbox” in a 1:1 ratio. We will randomise ICUs using a block randomisation, with randomly permuted blocks of two or four each consisting of an equal number of interventions and controls. A researcher, who is otherwise unaffiliated with the study and blinded to the identity of the units, will perform the randomisation according to a computer-generated random schedule produced using an R script (R Foundation for Statistical Computing; Vienna, Austria) before the study starts. The size and the contents of the randomisation blocks will be concealed from the investigators enrolling the ICUs. Participants will not be told explicitly what aspect of the intervention is randomised; they will only be aware that there are two variations of providing A&F. Due to the character of the intervention, it is not possible to blind the investigators.

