### Sample size

Sample size calculations for the RCT were based on pilot data of pain measurements from six ICUs (five teaching and one non-teaching) in 2014. Based on these data, the mean performance score for pain management is expected to be 76% with a standard deviation of 0.05%. We assumed a cluster size of 300 patient shifts per ICU per 3 months (3 months × 10 average number of patients × 10 average length of stay in shifts). The control arm, receiving only A&F, is expected to increase performance by a median of 4.3% (absolute improvement) based on the Cochrane review of previous A&F studies [18]. To have 80% power to find a difference in performance score for pain management of 10% using a two-sided unpaired *t* test with α = 0.05 would require a total of 24 ICUs to participate in the study.

We did not perform a sample size calculation for the laboratory experiment (study part 1) because this experiment will be conducted in the context of the RCT.

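### Too few ICUs is not a sound reason to forgo stratifying by hospital type: two strata with the plan's own block sizes work at 24 ICUs, and the stated fallback is a weak, inconsistently defined substitute

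*Protocol article*

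**What the plan says.** Under Randomisation and allocation: "We will randomise ICUs using a block randomisation, with randomly permuted blocks of two or four". This is one list at 1:1, with no stratification factor.

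The Strengths and limitations section takes up hospital type. It notes that "there is some evidence that non-teaching hospitals use pain assessment tools more often than teaching hospitals", grants that stratifying "would equalise the distribution of hospital types over the two arms in the RCT" and so would prevent confounding by it, and then sets the option aside because "we expect there will be insufficient participants to do so". In its place it offers a sensitivity analysis if the arms prove imbalanced at baseline.

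The Statistical analysis section counts hospital type among "baseline variables that may influence the outcome". There, imbalance is tested only if a problem with the randomisation is suspected, and an adjusted sensitivity analysis follows only if the imbalance is significant at the 5% level. The primary model has time, arm and time by arm, with random effects for ICU, patient and shift.

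The Sample size section says that its target "would require a total of 24 ICUs to participate in the study".

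**The concern.** The protocol supplies the argument for stratifying and rejects it on one ground, the number of ICUs. Sparse strata are a real problem when several factors are crossed. Here there is one factor with two levels, and the blocks are already small. If the ground is wrong, the trial accepts an avoidable chance of arms that differ visibly on a factor which the authors themselves think may matter. It then relies on a fallback that may not operate when the split is uneven. At stake are the precision and credibility of a comparison with about 12 ICUs per arm.

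**Working it through.** **Inputs.** 24 ICUs, 1:1 (Sample size; Randomisation and allocation). Blocks of two or four. The Setting section gives 32 teaching and 51 non-teaching ICUs in the registry. The enrolled mix is not known. At the registry mix, 24 × 32/83 = 9.25, so 9 teaching and 15 non-teaching are assumed, with other mixes shown as a range.

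**The plan's figure of 24.** A 10-point difference with an SD of 0.05 on the proportion scale needs only 6 ICUs per arm by *t* test. The 24 is reached if 10 points is the toolbox arm's gain from 76% and the control arm gains 4.3 points (80.3% versus 86.0%). With an implied ICC of 0.05²/(0.76 × 0.24) = 0.0137 and 300 shifts per ICU, 676 × (1 + 299 × 0.0137)/300 = 11.5, so 12 per arm. That is a reading, not a printed derivation. The present point needs only the total of 24.

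**Is stratification feasible?** Within a stratum only the last block can be incomplete, and an incomplete block of four is out of balance by at most 2. The gap is therefore at most 2, whatever the stratum's size. With 9 and 15 ICUs the gap must also be odd, so the splits are 5:4 and 8:7. When the number of teaching ICUs is drawn from the registry pool, simulation (20,000 replicates) gives the following for one list per hospital type:

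| Total ICUs | Largest gap in teaching ICUs | P(gap of 2) |
|---|---|---|
| 24 | 2 | 5.5% |
| 20 | 2 | 5.7% |
| 16 | 2 | 5.5% |

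**What does the single list leave open?** With 12:12 arms and 9 teaching ICUs, the number of teaching ICUs in one arm is hypergeometric:

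- P(5:4 either way) = 2 × C(9,4) × C(15,8)/C(24,12) = 2 × 126 × 6435/2,704,156 = 0.600, so P(6:3 or worse) = 0.400.
- P(7:2 or worse) = 2 × (36 × 3003 + 9 × 1365 + 455)/2,704,156 = 0.089.
- P(8:1 or worse) = 2 × (9 × 1365 + 455)/2,704,156 = 0.009.

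With 6, 10 or 12 teaching ICUs, P(gap of 4 or more) is 15.5%, 21.4% and 22.0%. With the number drawn from the registry pool, simulation of the single block list gives a gap of 3 or more in 30% of allocations and 5 or more in 6%. Stratified, a gap of 3 or more never occurs.

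**Would the fallback operate?** The plan names no test, so both usual choices are shown for 12:12 arms:

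| Split | Fisher p | Chi-square p, uncorrected |
|---|---|---|
| 6:3 | 0.40 | 0.21 |
| 7:2 | 0.089 | 0.035 |
| 8:1 | 0.009 | 0.003 |

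A 6:3 split is missed by either test. A 7:2 split is caught by chi-square and missed by Fisher. Under the Statistical analysis section, no test is run at all unless something is thought to have gone wrong with the randomisation, and chance imbalance is not such a fault. Under Strengths and limitations, baseline imbalance alone is enough. The two triggers are different rules.

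**Size of the effect.** The documents give no teaching versus non-teaching difference. If it is 2 to 5 points in level (assumed), a 7:2 split shifts the comparison of arm levels by 5/12 of that, 0.8 to 2.1 points. A 6:3 split shifts it by 3/12, 0.5 to 1.25 points.

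**The case against.** The strongest reply is that chance imbalance under concealed randomisation does not inflate type I error, that variation between ICUs, including any due to hospital type, is already in the SD used for planning, and that the authors disclose the limitation. All of that stands.

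A second reply is that the primary model targets time by arm with ICU random effects, so a stable difference in level largely cancels. That also stands: the shifts above concern arm levels and overstate the effect on the planned contrast. Harm arises mainly if hospital type also affects change over time. The documents do not say that it does, although the Background reports that feedback may work better where baseline performance is low.

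A reader might infer something stronger: that a 7:2 split could produce most of the effect sought. At an assumed 10-point difference the level shift would be 10 × 5/12 = 4.2 points. The documents do not support that reading. With a 9/15 mix, a 10-point difference alone implies a between-ICU SD of 10 × √(0.375 × 0.625) = 4.8 points, about 94% of the variance if the planning SD is 5 points. The printed target is 10 points; 5.7 (10 − 4.3) is only an inference. Nor does the plan establish hospital type as prognostic. It cites some evidence on the use of assessment tools, which bears most directly on the measurement indicator, a secondary outcome.

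The enrolled mix is also uncertain: participation is voluntary, and the six pilot ICUs were five teaching and one non-teaching. This changes the probabilities, but not the cap of 2 under stratification.

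**Conclusion.** The reason given for not stratifying is wrong at 24 ICUs, and would be wrong at 16. Stratifying would hold the gap in teaching ICUs to at most 2. The single list allows 6:3 or worse with 40% probability and 7:2 or worse with 8.9%, assuming 9 teaching ICUs, 12:12 arms and an order of enrolment unrelated to the allocation list. The significance-triggered fallback would miss 6:3, and its two descriptions need to be reconciled. The consequence is a loss of precision and credibility. It does not make the trial invalid, and no bias of a known size follows from it. The change is worth making because it costs almost nothing.

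**What to change.** Generate two concealed block lists, teaching and non-teaching, from the same R script. Prespecify hospital type and hospital type by time as covariates in the primary model, and drop the significance-triggered adjustment. The interaction is needed because a main effect alone would barely alter a time by arm coefficient when ICU random effects are already in the model. If allocation is already complete, leave it as it is and use the prespecified covariates alone. Give one rule for baseline imbalance in both sections.

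The cost is one more list, one or two more model parameters, and slightly looser overall arm balance: in simulation at 24 ICUs the arm sizes differ by 0.7 on average and 4 at most, against 0.2 and 2 for the single list. The researcher who runs the allocation must be told each unit's hospital type, but can stay blind to its identity.
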